## Abstract

**Background:**

With age, most cognitive functions decline. As the number of people aged 60 years and older is expected to rise rapidly within the next decades, identifying interventions that promote healthy cognitive ageing is of utmost importance. Promising research on bilingualism has led to the notion that learning a foreign language could protect against cognitive decline. Foreign language learning likely promotes executive functions, which are higher-order cognitive abilities particularly affected by age-related cognitive decline. However, evidence is still sparse and has produced contradictory results. This study aims to investigate the effects of short and intensive foreign language learning on executive functions in healthy older adults.

**Methods:**

In a randomised controlled trial, we will assign 60 native German-speaking monolingual healthy older adults, aged 65–80 years, to either a foreign language learning or a waiting list control group. Language learners will attend a face-to-face, group-based Spanish course for beginners for 1.5 h a day, 5 days a week, for a total of 3 weeks. Cognitive performance in executive functions will be assessed before and after the intervention or after a waiting period of 3 weeks (waiting list control group). Participants will be tested again after 3 months to evaluate longitudinal effects of foreign language learning. The waiting list control group will receive Spanish lessons only after the final assessment and will be invited to an additional voluntary evaluation after completion of the course.

**Discussion:**

To the best of our knowledge, we are conducting the first randomised controlled trial on the effects of short and intensive foreign language learning in older adulthood on executive functions. Enhanced cognitive performance after foreign language learning would indicate that learning a foreign language could enlarge cognitive reserve and thus promote healthy cognitive ageing in older adults.

**Trial registration:**

German Clinical Trials Register DRKS00016552. Registered on 11 February 2019.

## Background

The number of people aged 60 years or older will more than double worldwide to around two billion by 2050 [1]. With age, the majority of cognitive functions decline [2]. This not only threatens individual independence but can also enter pathological stages such as mild cognitive impairment and dementia, in its most severe form [3]. Cognitive ageing concerns a wide range of cognitive functions. Among these, executive functions (EF) are most markedly affected [2]. EF are a set of higher-order cognitive abilities that are involved in the control of mental activities and behaviour and are predominantly seated in the prefrontal cortex [4]. However, cognitive decline proceeds not linearly, because it is impacted by numerous variables. These include not only genetic and medical [5], but also psychosocial factors such as education and intelligence [6]. Moreover, cognitive benefits have already been documented for a variety of cognitively stimulating mental activities in older age such as playing the piano [7] or video gaming [8] (see [9] for a review, see also [10]). Mental activity builds up a cognitive reserve, which is a presumed mechanism for coping with age-related brain damage through a more effective and flexible use of cognitive networks [11]. Interest in foreign language learning as a cognitively stimulating mental activity later in life has only recently emerged and could constitute a promising approach to benefit cognitive functioning.

The idea of investigating foreign language learning as a powerful candidate for enhancing cognition in later life originated from research on bilingualism. Bilingualism can be defined as the ability to speak two languages fluently [12]. It has been associated with better cognitive performance compared to monolinguals, particularly in EF [13, 14]. Moreover, bilinguals exhibit slower cognitive ageing [15]. This so-called ‘bilingual advantage’ in EF probably arises from the demands placed on the cognitive control system by handling two languages. For example, although only one language is being used, both are always simultaneously active in the brain. Therefore, interference caused by the irrelevant language must be inhibited (see [16] for a review). Evidently, foreign language learning differs from bilingualism in important aspects, e.g. in the degree of proficiency. Nevertheless, foreign language learning is likely to promote EF in a comparable way, since language learning also engages an extensive cortical and sub-cortical brain network [17, 18]. This network is responsible for the control of both linguistic and non-linguistic information [19], and overlaps with the network affected by cognitive decline [20]. In initial stages of foreign language acquisition, the left inferior frontal gyrus of the prefrontal cortex is likely to play a major role [18]. Especially when it comes to producing the weaker (foreign) language, this gyrus is involved in the regulation of automatic processes that require attentional control. These processes include inhibition, interference or response selection and suppression [17]. Importantly, attentional dysregulation is probably also contributing to age-related deficits in other cognitive domains such as task switching or response competition [2]. For this reason, foreign language learning could enhance cognitive functions that are particularly affected by cognitive decline.

So far, however, research on cognitive outcomes of foreign language learning in older age is still sparse and has produced mixed results. In a small review summarising results of studies involving a foreign language training intervention [21], five papers [22–26] investigated cognitive outcomes before and after a language course intervention. After adding three more recently published studies to this overview [27–29], no clear cognitive advantage of foreign language learning became evident. Half of the studies detected benefits in one or more cognitive domains, including attentional switching [26], inhibition [24], working memory [29], and global cognition [27, 29]. In contrast, others found no effect on spatial and verbal intelligence [22], working memory [22], task switching [23], and global cognition [25, 28]. This inconsistent picture could be due to several reasons. Overall, there was little overlap between cognitive domains and tasks applied among studies. Interestingly, studies focusing on EF tasks that required high amounts of attentional control were among those showing significant improvements in cognition after foreign language learning [24, 26]. Studies also differed considerably in their effectiveness depending on the design of the intervention. For example, studies with shorter (e.g. 1 week [26]) but higher intensity interventions (at least 5 h of training per week, spread over several days a week) [24, 26] were more consistently associated with cognitive improvements than studies with longer but less intensive interventions [25, 28]. Thus, studies with a higher-intensity foreign language training might be more likely to affect cognition. It is also important to note that some previous studies exhibited limitations, e.g. lack of a control group [24, 25], no randomised group allocation [23, 26], lack of follow-up periods [22–25, 27, 28] and missing control of cognitive impairment [24–26]. These should be considered in future studies. We therefore decided to conduct a randomised controlled trial with high-intensity training and comprehensive control of cognitive impairment to determine whether foreign language learning can improve EF in older adults.

## Methods/design

### Aims

The objective of the present study is to assess the effects of short and intensive foreign language learning on EF in healthy older adults. We hypothesise that, compared to a passive control group, foreign language learning improves EF (hypothesis 1), and that these effects persist in the long-term over 3 months after the intervention (hypothesis 2). To test our hypotheses, we will focus primarily on two tasks affording a high degree of attentional control, since foreign language learning is likely to address this fundamental process of EF. However, as this field still is largely unexplored, we will additionally consider a wider range of EF, including inhibition, shifting, and updating, as the most commonly accepted EF [30]. Moreover, we will evaluate domains that can broadly be classified as EF, but which equally cover linguistic functions (verbal fluency) and non-executive components of attention.

To further explore our results, we will also assess the role of cognitive reserve, as different levels of cognitive reserve have been shown to influence training-related changes in global cognition [31]. This might also apply for previous foreign language knowledge and usage. Therefore, we assume that both the degree of cognitive reserve (hypothesis 3) and prior foreign language knowledge and usage (hypothesis 4) can predict changes in cognitive scores.

### Study design and setting

The present study is a randomised controlled superiority trial with two parallel groups which investigates the effects of a three-week-long foreign language course on EF in healthy older adults. Sixty community-dwelling older adults will be randomised in a 1:1 ratio to one of two study arms: a language learning group (LLG) and a waiting list control group (WLCG). Data will be collected at the Network Aging Research (NAR), Heidelberg University, Germany and the SRH University Heidelberg, Germany. This study protocol follows the Consolidated Standard of Reporting Trials (CONSORT) statement [32] and is presented according to the Standard Protocol Items: Recommendations for Interventional Trials (SPIRIT) guidelines [33].

### Recruitment

Participants will be recruited from the general public in Heidelberg, Germany, and the surrounding regions through advertisements in local newspapers, advertising in trains, at public lectures, and on the NAR homepage. We will also inform individuals who agreed to be notified about ongoing studies via an e-mailing list of the NAR. Additionally, we will distribute flyers and posters in senior and sports centres, language schools, medical practices, and pharmacies.

### Eligibility criteria

Eligibility criteria for participation are listed in Table 1.

**Table 1 Tab1:** Eligibility criteria for participation

Inclusion criteria	Aged between 65 and 80 years
	Native language German
	Living independently
	Motivated to participate; Signing written informed consent for study participation confirmed by the local ethics committee
Exclusion criteria	Spanish level ≥ A1.1 according to the Joint European Reference Frame for Languages or having already attended a regular Spanish course for beginners (≥ 18 h of teaching)
	Bilingualism or multilingualism (def.: fluent command [level ≥ C1 as defined by questions derived from the Joint European Reference Frame for Languages] and frequent usage of any foreign language)
	Any Romanic language (French, Italian, Latin, Portuguese) level ≥ B1 (as defined by questions derived from the Joint European Reference Frame for Languages)
	Cognitive functions below cut-off (Cognitive Functions Dementia [CFD] [34, 35]: no subtest *z* ≤ − 1.5 [36]) according to age and where possible additionally to sex and education
	Impaired/not-corrected vision
	Colour blindness
	Wearing a hearing aid or impaired sense of hearing as measured by the whispered voice test [37]
	Part-time employment with 20 or more hours of working activity per week
	Self-reported former or current neurological disease (e.g. stroke, mild cognitive impairment, dementia, Parkinson’s disease, epilepsy, multiple sclerosis, encephalitis, cerebral tumour)
	Self-reported current/diagnosed mental health disorder (e.g. anxiety disorder, major depression, schizophrenia, alcoholism or other addiction)
	Transient loss of consciousness for more than five minutes
	Current musical activity for more than five hours per week
	Psychotropic medication within the last six months before the start of the study
	Surgery within the last month before the start of the study
	Other constraints hindering attendance at both the assessments and intervention appointments

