#### Waiting list control group (WLCG)

The WLCG will not receive any treatment during the intervention phase but will take part in a three-week waiting period during which subjects will follow their usual daily routine. To reduce barriers to participation due to possible group preferences [40], the WLCG will attend a control group programme after their study completion. The programme consists of the same language course intervention as the LLG and an additional voluntary examination after the end of the course. This appointment is not included in the main study design as the scope for participation should differ as little as possible between groups.

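### Current language learners are eligible and controls' language learning is neither restricted nor recorded, so the passive arm can contain the exposure and weaken the contrast by an unknown, probably modest amount

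*Protocol article*

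**What the plan says.** Under Aims, the first hypothesis is that, "compared to a passive control group, foreign language learning improves EF (hypothesis 1"; the second extends this to 3 months after the intervention.

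Table 1 (Eligibility criteria) has three language exclusions:
- Spanish: level A1.1 or above, or "having already attended a regular Spanish course for beginners (≥ 18 h of teaching".
- Romance languages: "Any Romanic language (French, Italian, Latin, Portuguese) level ≥ B1".
- Bilingualism: fluent command at C1 or above "and frequent usage of any foreign language". Both parts must be met.

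No line asks whether a person is learning a language now. One line does limit a current stimulating activity: "Current musical activity for more than five hours per week".

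Under Recruitment, "we will distribute flyers and posters in senior and sports centres, language schools, medical practices, and pharmacies". Controls have a three-week waiting period "during which subjects will follow their usual daily routine" (Waiting list control group). They receive the Spanish course only after the 3-month assessment.

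Under Homework and learning time, home study is recorded for Spanish only, from the first to the last day of the course. Under Statistical analysis, the only stated use of the LSBQ score is a regression within the language learning group (hypothesis 4). The two sensitivity analyses concern protocol adherence and missing values.

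**The concern.** The comparison is meant to be language learning against none. A control who attends a language class during the waiting period, or in the three months to follow-up, is not passive in that sense. A current learner assigned to the Spanish course may gain less from it than someone new to language study. Either would pull the group × time interaction towards zero.

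This would cost power rather than create a false positive. It matters because the Discussion calls the existing evidence contradictory and presents this trial as a well-controlled answer. If the result is null, the authors could not say how much language learning took place in the control arm, because nobody will have asked.

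**Working it through.** **1. Who passes Table 1.**

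| Person | Rule that might apply | Excluded? |
|---|---|---|
| Weekly English class, level B2 | C1 with frequent use | No |
| Beginner in French or Italian | Romance language at B1 or above | No |
| Part-way through a first Spanish course, under 18 h and below A1.1 | Spanish A1.1 or 18 h | No |
| Any of these with a timetable clash | Availability | Possibly |

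**2. Whether the plan would notice.** Controls have no study log. The LSBQ and the telephone screening are described as covering skills and usage, not course attendance. No question about language learning is described at post or at 3 months. As described, the exposure could not be reconstructed at analysis.

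**3. The plan's own sample size.** Inputs from Sample size and Statistical analysis: α = 0.05 two-sided, Bonferroni over two primary outcomes (0.025 each), power 0.80, effect 0.25, r = 0.5, two groups, pre and post. For a repeated-measures within-between interaction with m = 2 time points:

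λ = f² × N × m / (1 − r), with 1 and N − 2 degrees of freedom.

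At f = 0.25 and N = 42, λ = 0.0625 × 42 × 2 / 0.5 = 10.5 and power is 0.815. N = 42 reproduces, provided the printed 0.25 is read as Cohen's f; the text labels it d.

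**4. Attenuation.** Let p be the share of current learners, equal in both arms in expectation, and h the fraction of the contrast lost among them. The expected contrast is (1 − p) + p(1 − h) = 1 − ph times its full value. The documents give neither p nor h, so both are assumptions. h = 1 is the worst case, unless current learners did worse on Spanish than without it. The same formula holds if a share p of controls alone obtains a fraction h of the intervention effect.

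Sample inflation is 1/(1 − ph)². Power is recomputed with f = 0.25 × (1 − ph):

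| p | h | Factor | Inflation | Power at N = 42 |
|---|---|---|---|---|
| 0 | – | 1.00 | 1.00 | 0.815 |
| 10% | 0.5 | 0.95 | 1.11 | 0.770 |
| 10% | 1 | 0.90 | 1.23 | 0.720 |
| 20% | 0.5 | 0.90 | 1.23 | 0.720 |
| 20% | 1 | 0.80 | 1.56 | 0.606 |
| 30% | 0.5 | 0.85 | 1.38 | 0.665 |
| 30% | 1 | 0.70 | 2.04 | 0.482 |

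Example: p = 10%, h = 1 gives 1 − 0.10 = 0.90 and 1/0.90² = 1.23. The rows with h = 1 bound the loss for each p; they are not estimates.

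**The case against.** The strongest reply is that the trial tests a short, intensive beginners' course of 7.5 h a week, not language learning of any kind. The Background says that longer, less intensive courses were less consistently linked to benefit. A weekly English class is therefore not the intervention, and randomisation preserves a clean contrast: usual routine plus intensive Spanish against usual routine. The analysis also tests change from pre-assessment, so a course already running may be absorbed in the pre-score. This stands, and it is why h = 1 is a ceiling. It does not cover a course begun near or after pre-assessment, and hypothesis 1 is worded as foreign language learning in general.

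There are partial barriers. Table 1 excludes "Other constraints hindering attendance at both the assessments and intervention appointments", and lessons are on weekday mornings. People with slight Spanish take a placement test. Controls are promised a free course later. Language schools are one of about ten recruitment channels. These lower the likely share but leave afternoon, evening and self-study learners eligible. It cannot be assumed that a longer document closes the gap, because Data Availability describes this article as the full protocol.

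A reader might infer more than the text supports:
- *That the contrast is in fact diluted.* No share of current learners is given, and no loss of benefit among them is shown.
- *That allowing just under 18 h of earlier Spanish admits more than the 14 h treated as an active amount.* This is not like for like. The 14 h came from one intensive week and is reused as a per-protocol minimum within the course. The 18 h limit concerns past teaching over an unstated period, which randomisation balances in expectation and which does not make the control arm active.
- *That the music rule is a precedent for a total ban.* It permits up to five hours a week. It shows only that a current activity was considered.

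**Conclusion.** The gap is real. People currently learning a language below the stated levels are eligible, and language study in controls is neither restricted nor recorded over the waiting period or the three months to follow-up. The arm called passive can therefore contain undetected language learning, and a null result would be harder to read.

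The size is unknown. For a given share p the contrast keeps at least (1 − p) of its value: 0.90 at an assumed 10%, with power at 42 evaluable participants falling from 0.815 to no lower than about 0.72. The likely loss is smaller. These figures rest on assumed values of p and h, on reading 0.25 as Cohen's f, and on ignoring the small extra variance of a mixed group. The documents do not support saying that the trial is compromised or that a null result would be uninterpretable. The point is a cheap improvement that has to be made while participants can still be asked.

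**What to change.** 1. Ask participants in both arms directly whether they are attending a language course or studying a language on their own (language, hours per week, start date). Ask at baseline, at post and at 3 months.
2. Put the baseline question retrospectively to those already enrolled (54 of 60 under Trial status), since the LSBQ and the telephone screening are not described as covering it. Do this before the data are anonymised. These participants know their allocation, so ask for facts such as course and dates.
3. Ask the waiting list group not to start a language course before the 3-month assessment. No matching request to the language learning group is needed.
4. Pre-specify a sensitivity analysis of both primary outcomes that excludes participants who were learning a language at baseline. Because the exclusion uses baseline status, the randomised comparison is kept. Report learning after baseline descriptively by arm, and do not exclude on it.
5. Optionally, add an exclusion for current learners. It would reach only the last 60 − 54 = 6 places and is not essential.

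Cost: one short question at existing visits, one contact with enrolled participants, and one more analysis on a smaller set (at an assumed p of 10%, 60 × 0.90 = 54 before drop-out).

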### Interventions

This study comprises two trial arms: a LLG and a WLCG.

#### Language learning group (LLG)

The LLG will study Spanish in a three-week course for beginners. Daily lessons of 90 min will be scheduled in the morning from Monday until Friday. In sum, participants will receive 7.5 h of teaching per week, resulting in a total course duration of 22.5 h. The idea of a relatively short but high-intensity training stems from a study by Bak et al. [26], who found a positive effect of foreign language learning on attentional switching after only 1 week of 14 h of foreign language instruction.

A qualified teacher will give the lessons face-to-face at a language school in the centre of Heidelberg, which is easily accessible by car and public transportation. Beyond attending regular classes, participants may do homework and will be allowed to practice at home to consolidate the newly learned content. Following the example of previous studies [23, 38], we will limit the group size to a maximum of ten participants per group, to enable the teacher to address all participants and to give them sufficient opportunity to participate in class. A commonly used work book in adult education [39] will serve as teaching material. By the end of the course, approximately three chapters will have been completed. Participants will learn accent and pronunciation as well as grammatical rules of the Spanish language and will acquire elementary communication skills in various topics (e.g. introducing themselves, asking for directions).

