### Sample size

Sample size calculation was based on the main (first) research question for the two primary outcomes, the STROOP and the WAFG, and was conducted using G*Power (version 3.1.9.2). The alpha level was set to α = .05 with the power to detect significant differences of 0.8. A total of *N* = 42 participants will be needed to detect a medium effect size of *d* = 0.25 [24, 26, 62] between pre- and post-assessment, assuming a correlation between repeated measures of *r* = .5. We will adjust for multiple comparisons using the Bonferroni correction. A total sample size of *N* = 60, with *n* = 30 individuals per group, will be required to account for a 30% drop-out rate [24].

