### Statistical analysis

Statistical analysis will be conducted using IBM SPSS Statistics 26 (IBM Corporation: Armonk, NY, USA). We will use the intention-to-treat dataset, considering all participants as randomised who have completed at least pre-assessment and regardless of adherence to protocol. Hypotheses will be tested two-sided on an alpha level of α ≤ .05, which will be adjusted for multiplicity for primary outcomes by applying the Bonferroni correction. Multiple imputation techniques will be applied to account for missing data assuming that data are missing at random (MAR). Additionally, we will report reasons for withdrawal and analyse them qualitatively.

Primary and secondary outcomes will be analysed using 2 (group) × 3 (time) repeated measures analysis of variance (ANOVAs) with group as between-subjects factor and time-point of assessment (pre-, post-, 3-month follow-up) as within-subjects factor. Bonferroni’s post hoc test will be conducted to test hypotheses. We predict a significant group x time interaction, in which the LLG will outperform the WLCG at post- compared to pre-assessment (hypothesis 1) and at 3-month follow-up compared to pre-assessment (hypothesis 2). Partial eta square (*η*_*p*_^2^) will be used as an indicator of effect size.

For the LLG, exploratory subgroup analyses will be performed to evaluate whether effects of foreign language learning on cognitive outcomes are dependent on different levels of cognitive reserve (hypothesis 3) and foreign language knowledge and usage (hypothesis 4). Therefore, we will conduct multiple and simple regression analyses, respectively. The difference in primary outcome measures between pre- and post-assessment will be defined as the dependent variable. Age and indicators of cognitive reserve (CRI-Education, CRI-WorkingActivity, CRI-LeisureTime, and CRI-Index) (hypothesis 3) and the LSBQ-score (hypothesis 4) will be considered as independent variables.

Additionally, we will investigate whether short-term effects of foreign language learning on cognitive measures also apply to the WLCG after completing the control group programme. For this purpose, the WLCG will serve as its control. Using *t*-tests for dependent means, we predict a significant difference between the difference scores from 3- to 4-month follow-up compared to the difference scores from pre- to post-assessment.

To assess the robustness of results, we will perform sensitivity analyses for the following:

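### The course is taught in small classes in one arm only, but the ANOVA and sample size treat all participants as independent; the size of the effect depends on a class correlation the protocol does not give

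*Protocol article*

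**What the plan says.** Randomisation is individual: "Sixty community-dwelling older adults will be randomised in a 1:1 ratio to one of two study arms" (Study design and setting). The learning arm is then taught in groups. The Language learning group section says "A qualified teacher will give the lessons face-to-face at a language school in the centre of Heidelberg" and adds that "we will limit the group size to a maximum of ten participants per group". The other arm has no comparable grouping: "The WLCG will not receive any treatment during the intervention phase" (Waiting list control group).

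The Statistical analysis section fixes a two-by-three repeated-measures ANOVA for all primary and secondary outcomes, "with group as between-subjects factor and time-point of assessment (pre-, post-, 3-month follow-up) as within-subjects factor". It has no class or wave term. The two sensitivity analyses listed concern non-adherence and missing values.

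The Sample size section says "The alpha level was set to α = .05 with the power to detect significant differences of 0.8". Its other inputs are an effect size of 0.25, a repeated-measures correlation of .5, a Bonferroni adjustment and 30% drop-out. It ends with "A total sample size of *N* = 60, with *n* = 30 individuals per group". It mentions neither an ICC nor a design effect.

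**The concern.** Classmates share a room, peers and daily lessons for three weeks. If those shared conditions move their test scores together, 30 learners carry less information about the average course effect than 30 independent people. The waiting group has no such structure during the comparison, so only one arm is affected.

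The ANOVA takes its error term from variation between individuals. Any variation between classes in the mean gain would then be read as information about the course. A result just under the Bonferroni threshold could reflect one class that did unusually well, and the plan has nothing that would show this. The protocol names the model and its factors, so the point concerns a stated choice and is not a detail left to a later document.

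**Working it through.** **Reproducing the plan's figure.** G*Power's within-between interaction uses λ = f²·N·m/(1 − r), with df = (m − 1) and (N − 2)(m − 1). Take f = 0.25, r = .5, two groups, m = 2 time points and α = .05/2 = .025.
- N = 42 gives λ = 0.0625 × 42 × 2/0.5 = 10.5 on 1 and 40 df, and power 0.815.
- 42/0.70 = 60, as stated.

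The plan's N therefore matches a calculation on independent participants with no design effect. (The match requires 0.25 to be read as Cohen's f, although the text labels it d. That is a separate matter.)

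**Inputs for the check**
- Class size: ten is the stated maximum, and 30/10 = 3 classes at least. If 30% drop out, 21 learners remain, or 7 per class in three classes.
- Test level per primary outcome: .025, two-sided, so z = 2.2414.
- ICC of change within classes: not in the document. Assumed values are 0.01, 0.02, 0.05 and 0.10.

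**Formulas.** With c learners per class, DE = 1 + (c − 1)·ICC applies to the learning arm only. With equal arms, the variance of the group difference is multiplied by V = (1 + DE)/2 and its standard error by √V. The actual error of the unadjusted test is 2·[1 − Φ(2.2414/√V)].

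| Class size | ICC | DE | V | √V | Actual error at nominal .025 |
|---|---|---|---|---|---|
| 10 | 0.01 | 1.09 | 1.045 | 1.02 | .028 |
| 10 | 0.02 | 1.18 | 1.09 | 1.04 | .032 |
| 10 | 0.05 | 1.45 | 1.225 | 1.11 | .043 |
| 10 | 0.10 | 1.90 | 1.45 | 1.20 | .063 |
| 7 | 0.01 | 1.06 | 1.03 | 1.01 | .027 |
| 7 | 0.02 | 1.12 | 1.06 | 1.03 | .029 |
| 7 | 0.05 | 1.30 | 1.15 | 1.07 | .037 |
| 7 | 0.10 | 1.60 | 1.30 | 1.14 | .049 |

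A simulation of the unadjusted test with three classes (200,000 runs) gave .028, .043 and .062 for classes of ten at ICC 0.01, 0.05 and 0.10. For classes of seven it gave .027, .037 and .049. Smaller classes weaken the effect: for five classes of six at ICC 0.05, V = (1 + 1.25)/2 = 1.125 and the error is about .035.

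**Power.** The planned effect has a standardised size of √λ, which is √10.5 = 3.24 with 42 evaluable and √15 = 3.87 with 60. Normal-approximation power for a correctly scaled test is Φ(√λ/√V − 2.2414).
- 42 evaluable, seven per class, ICC 0.05: Φ(3.24/1.072 − 2.241) = 0.78, against 0.84 with no clustering.
- 60 evaluable, ten per class, ICC 0.05: Φ(3.87/1.107 − 2.241) = 0.90, against 0.95.

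**Evaluable N in place of 42** (21·V per arm, rounded up). At ICC 0.05 it is 50 with seven per class or 52 with ten per class. That means 72 or 75 randomised at 30% drop-out, before any correction to the degrees of freedom.

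**Cost of estimating the class effect.** With three classes and ICC 0.05, Satterthwaite degrees of freedom are about 5.5 to 6, and power falls to about 0.67 (60 evaluable) or 0.55 (42 evaluable). If each wave held a single class and wave were also fitted, three waves would leave 2 df, and power would be about 0.28 or 0.22.

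**The case against.** The strongest reply is that nothing in the document shows that class effects exist. A reader might infer that the outcomes are clustered, that the standard errors are too small, and that type I error exceeds its nominal level for both primary outcomes. The document does not support that as fact, for four reasons.

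- **No ICC is given.** The primary outcomes are individually administered computer tests of interference and divided attention. They are not language skills, on which class pace would act directly. A very small ICC for change is credible, and at 0.01 the issue is negligible.
- **The null matters.** If the course changes nobody's score, class membership changes nothing either, and individual randomisation protects the test. Type I error is inflated only when classes have differing effects that average to zero. Where the course works, the damage is to interval width and power.
- **Some sources of clustering may be absent.** The teacher is mentioned in the singular. One teacher for every class would add no variation between classes. Workbook, hours and school are common to all. If the waiting group waits over the same dates as the classes, date effects are largely shared by both arms. The document does not settle the number of teachers or the alignment of dates.
- **A class term is costly.** A reader might conclude that a random class effect belongs in the primary model. With about three classes, the power figures above argue against that. A class or wave term on level would also miss the target, because the hypotheses concern change.

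All four points stand. They make the claim conditional and limit the remedy. They do not remove the mismatch between teaching in classes and a model that assumes independence, and peer effects within a class remain possible.

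**Conclusion.** The point holds in conditional form. The design is partially nested, and both the ANOVA and the sample size assume independent participants in both arms. With a positive class ICC for change, the standard error of the group difference in change is understated by a factor of about 1.04 to 1.20 for classes of ten and ICC 0.02 to 0.10. The nominal .025 test then runs at about .032 to .063, or .029 to .049 with classes of seven, under a null in which class effects vary around zero. These figures rest on assumed ICCs, equal arms, three equal classes and clustering in the learning arm only; more and smaller classes would reduce them. The true size is unknown. The matter is worth settling before analysis because it changes how a borderline primary result may be read, but it does not justify replacing the primary model.

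**What to change.** Keep the planned primary ANOVA and make three additions.

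1. Record class and course wave for each learner. The document does not say whether this is already done. Since the teacher documents attendance daily, it should be easy.
2. In the Statistical analysis section, pre-specify a sensitivity analysis for both primary outcomes. Multiply the variance of the group-by-time contrasts (pre to post, and pre to 3-month follow-up) by (1 + DE)/2, that is, the standard error by its square root. Use the observed class sizes and ICC values from 0.02 to 0.10. Report whether the conclusion changes, and at which ICC.
3. In the Sample size section, state that N = 42 and power 0.8 assume no class clustering.

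If a model with a class effect is fitted as well, label it exploratory. The effect must act on change (class by time, with wave by time), and small-sample degrees of freedom are needed.

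The cost is a little extra analysis and a less favourable statement of power. No further recruitment or assessment is needed.
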